# Expressive writing to reduce depressive and anxiety symptoms among sexual minority veterans: Study design for a pilot randomized controlled trial

**DOI:** 10.1016/j.conctc.2026.101650

**Published:** 2026-05-27

**Keywords:** Veteran, Sexual minority, LGBQ+, Expressive writing, Minority stress

## Abstract

**Background:**

Sexual minority veterans (e.g., gay, lesbian, bisexual) are at increased risk for depression and anxiety due in part to the experience of sexual minority stressors. However, few interventions target distress related to sexual minority stressors, and even fewer have been tested in Veterans Health Administration (VHA). Brief, easy to implement interventions, such as expressive writing-based interventions, that target distress related to sexual minority stressors are needed to reduce disparities in depression and anxiety.

**Method:**

We describe the design of a two-phase study consisting of an open trial and a pilot randomized controlled trial (RCT) comparing Expressive Writing on Minority Stressors (EWMS) and a neutral writing condition among sexual minority veterans. The EWMS protocol will be iteratively refined in a case series (n = 10) and then tested in a pilot randomized control trial (RCT; n = 54). Aims of the pilot RCT are to: 1) demonstrate feasibility and acceptability of study procedures and EWMS using quantitative and qualitative data; and 2) examine preliminary trends in depressive and anxiety symptoms to inform the design of a future, fully powered efficacy trial. Participants will be assessed at baseline, posttreatment, and 3 months after treatment. Qualitative exit interviews will be conducted to inform refinements to the intervention with an eye towards usefulness, satisfaction, and implementation.

**Conclusions:**

This pilot RCT will inform the first fully powered clinical trial to test an individually delivered intervention for sexual minority veterans to reduce depressive and anxiety symptoms associated with minority stress.

## Expressive writing to reduce depressive and anxiety symptoms among sexual minority veterans: study design for a pilot randomized controlled trial

1

Sexual minority veterans (i.e., veterans who identify as gay, lesbian, bisexual, queer or other minoritized sexual orientations) represent a high-risk population for psychiatric disorders. Compared with heterosexual veterans, sexual minority veterans are two times more likely to have depressive and alcohol use disorders, three times more likely to report lifetime suicidal ideation (SI) and have substance use disorders [1,2], and are more than twice as likely to die by suicide [3]. Moreover, compared with their non-veteran peers, sexual minority veterans have greater posttraumatic stress disorder (PTSD), depression, and anxiety symptom severity [4]. Thus, interventions that address contributing factors for the higher prevalence and severity of psychiatric disorders are urgently needed for members of this community.

Results from prior studies with a variety of samples [5,6], observational and experimental methods [7,8], and both cross sectional and longitudinal designs [5,9,10] have shown that exposure to minority stressors in part explains sexual minority individuals’ higher prevalence and severity of depression, anxiety, and other outcomes. Exposure to sexual minority stressors is associated with both universal stress reactions [5,11] and reactions specific to sexual minority lived experiences, such as identity concealment and expectations for rejection [5,12]. These stress responses contribute to increased risk of anxiety and depression, which in turn explain risk for high-risk health behaviors (e.g., substance use and suicide) [13]. Therefore, sexual minority stressors are critical targets for psychotherapeutic intervention.

However, few interventions specifically target distress related to sexual minority stressors, and most that exist are lengthy (i.e., 10 to 12 sessions) [14]. Interventions of this length tend to have higher attrition and are more difficult to implement due to limited trained staff and resources [15]. Additionally, most interventions targeting minority stress are offered in group formats leaving few options for individuals interested in one-on-one care [14,16,17]. Brief one-on-one interventions targeting distress related to sexual minority stressor exposure are needed for sexual minority veterans given their greater depression and anxiety prevalence and severity. Brief interventions are important because they can be disseminated broadly, are cost-effective, and can significantly improve sexual minority people's health [18]. They can also serve as an adjunct to existing treatment options for depression and anxiety and be implemented in settings with lower acuity, such as primary care.

## Expressive writing-based intervention

2

Expressive writing is a technique in which an individual writes about their thoughts and emotions related to a stressful experience in response to structured writing prompts. Research over the past 40 years has consistently shown that expressive writing can improve mental and physical health [[18], [19], [20], [21], [22], [23], [24], [25], [26], [27], [28], [29]]. The standard expressive writing paradigm involves writing between 3 and 5 times in response to a structured prompt for up to 30 min per writing occasion. Both quantitative and qualitative data indicate that writing about emotions and cognitions related to sexual minority stressors for at least 3 writing sessions reduces depression and anxiety symptoms among non-veteran sexual minority people [18,22,[30], [31], [32], [33], [34]]. Expressive writing on sexual minority stressors has reduced perceived stressfulness of the minority stressor [30], negative mood [18,22,31], identity concealment [22], and improved perceptions of social support [22,32].

Although expressive writing on sexual minority stressors has not been tested with sexual minority veterans, an expressive writing-based intervention, Written Exposure Therapy (WET) for PTSD, effectively reduces PTSD and depression symptom severity among veterans [24,35]. WET is being disseminated across Veteran Health Administration (VHA) clinics [23] and has been implemented in a range of treatment settings (e.g., primary care, specialty mental health, inpatient psychiatry). Notably, significantly fewer people drop out of WET than people who have received other evidence-based PTSD treatments [35]. It also requires less training for providers compared with other treatments. Based on abundant research indicating that expressive writing interventions are beneficial for reducing depression and anxiety and have been successfully implemented in VHA, an expressive writing intervention focused on sexual minority stressors may be a promising intervention for addressing the deleterious impacts of sexual minority stressors among veterans.

This paper describes the protocol and study design to refine and pilot an expressive writing intervention for sexual minority veterans, Expressive Writing on Minority Stressors (EWMS). As expressive writing on sexual minority stressors has only been implemented with non-veterans, we plan to conduct a formative open-trial case series with 10 sexual minority veterans to iteratively refine and optimize the writing prompts and delivery of the intervention (Phase I) prior to testing in a pilot randomized controlled trial (RCT) (Phase II). The aim of the trial is to examine the feasibility and acceptability of both the study design and the intervention. The second aim of the trial is to describe trends in depressive and anxiety symptoms over time to inform the design of a future, fully powered efficacy trial.

## Methods

3

### Trial design

3.1

This pilot RCT will use a two-arm 1:1 parallel RCT design. The trial will take place at [redacted for review]. Participants will be randomly assigned to EWMS or a neutral writing condition with a 1:1 allocation using a computer generated randomization block design. A statistician not involved in the evaluation or execution of the trial will use R to generate the randomization allocation. Block sizes will not be known to the PI to ensure concealment. Randomization will be conducted by study staff that are not involved in delivery of treatment or assessment. The primary outcomes of the trial will be feasibility of the trial design (i.e., recruitment rates, retention rates) and intervention (i.e., percentage of treatment completion) and acceptability of the intervention (i.e., treatment satisfaction, helpfulness, and usefulness). All results related to depressive and anxiety symptom outcomes will be interpreted as preliminary trends as the purpose of the trial is to establish feasibility and acceptability of the trial design and EWMS to inform the design of a future, fully powered efficacy trial. Assessments will be completed at baseline, posttreatment, and 3-month post treatment via telephone diagnostic interviews and online self-report questionnaires. The trial has been reviewed and approved by the Institutional Review Board at VA Boston Healthcare System and is registered with ClinicalTrials.gov NCT05897021.

### Participants

3.2

The total sample for the trial will include 64 sexual minority veterans who are at least 18 years of age. Phase I will include 10 sexual minority veterans and Phase II will include 54 sexual minority veterans. The inclusion criteria includes: (1) being a veteran (2) identifying as a sexual minority person (i.e., identifying as gay, lesbian, bisexual, pansexual, queer, or another identity other than heterosexual), (3) endorsing clinically significant depressive or anxiety symptoms (score above 10 on the Patient Health Questionnaire-9 [PHQ-9] [36] or the Generalized Anxiety Disorders-7 [GAD-7] [37]), (4) reporting a history of sexuality-based minority stressor exposure that is contributing to distress based on the endorsement of at least one item on the Everyday Discrimination Scale (EDS) [38] that is contributing to distress per veteran report (i.e., “Are you currently experiencing distress [e.g., sadness, anger, anxiety, etc.] related to any of the above [discrimination] experiences?”), and (5) if on psychotropic medication, being on a stable dose for at least 4 weeks. Exclusion criteria includes: (1) clear and current suicidal plan and/or intent (assessed via the Columbia Suicide Severity Rating Scale [C-SSRS] [39]), (2) current presentation of unstable mania and/or psychosis (assessed via the Structured Interview for DSM-5 [SCID]), (3) current substance use disorder, severe (assessed via the SCID [40]), and (4) significant cognitive impairment determined by an inability to comprehend baseline screening questionnaires.

### Procedures

3.3

#### Recruitment

3.3.1

Veterans will be recruited from local mental health clinics and primary care clinics at [masked] via referrals from clinicians or self-referred through fliers distributed throughout the hospital campuses. We will also recruit through local hospitals, veteran organizations, and LGBTQ + organizations via flyers, emails on listservs, and on social media to recruit veterans who may not already be receiving care at [masked].

#### Screening

3.3.2

See Fig. 1 for participant flow diagram. All interested potential participants will contact the research team to complete a phone screening to determine initial eligibility for the study. Initial eligibility will include: 1) being a veteran, 2) identifying as a sexual minority person, 3) experiencing a minority stressor that is contributing to distress, and 4) if on a psychotropic medication, on a stable dose for at least 4 weeks. If initially eligible based on the phone screening, potential participants will complete informed consent and complete the baseline assessment (diagnostic interview via phone and online self-report questionnaires) to determine eligibility for the study.

**Fig. 1 fig1:**
[figure not shown]
Participant flow diagram.

#### Measures

3.3.3

**Eligibility.** Following screening and consent, the PHQ-9 and GAD-7 will be used to assess for inclusion criteria (i.e., score above 10 on either). The SCID mood, psychotic, and substance use modules will be administered to assess current psychosis, mania, or severe substance use disorder. Additionally, the C-SSRS will be administered to assess the presence of current suicidal plan and/or intent.

**Feasibility.** Feasibility of the study design will be measured by the rate and number of referrals for the study and the retention rates for participants across study procedures. Level of feasibility of the intervention will be assessed by examining the percentage of treatment completion.

**Acceptability.** Participants will complete the Client Satisfaction Questionnaire (CSQ-8) [41] to assess treatment satisfaction. Study clinicians for the trial will complete the self-report measure assessing attitudes towards the intervention using the Evidence-Based Practice Attitudes Scale-50 anchored to EWMS [42]. The study team will conduct exit interviews with all veterans at the post-treatment assessment and with clinicians towards the end of Phase II. Consistent with treatment development and implementation considerations, interviews will assess veterans' and clinicians' perceptions of the feasibility, acceptability, usefulness and helpfulness of the intervention, cultural relevance and appropriateness of the intervention, as well as any recommendations for modifications to the intervention to improve the fit of the intervention for the patient population and VHA clinical setting [43,44]. Interviews will be audio recorded for transcription purposes and to inform development of the interview guide for the fully powered clinical trial. Some interview questions will be derived deductively by identifying categories at the beginning of the project. These areas will focus on participants’ perceptions of feasibility and acceptability of the EWMS intervention format and content (e.g., length of treatment, writing prompts). Other questions will be derived inductively by identifying emergent themes. Interview transcripts will be analyzed using a rapid content analysis approach widely used when developing and modifying interventions in VHA [45]. Data collected from the interviews in Phase I (open trial) will be used to inform modifications to the intervention protocol that will be tested in Phase II. Qualitative data collected during Phase II will be used to inform modifications to the protocol for future implementation and testing of the intervention.

**Preliminary Outcomes.** The primary preliminary outcomes are depression and anxiety measured with the PHQ-9 and GAD-7, along with the Depression, Anxiety, and Stress Scale [DASS-21] [46]. Although not the primary focus, the mood and anxiety modules of the SCID will be administered at each time point to describe the sample and allow us to determine whether participants meet criteria for depressive and anxiety disorders, in addition to their self-report measures. Regarding stressors, assessments will involve measures that assess trauma history (Life Events Checklist for DSM-5 [LEC-5] [47] and distal minority stressors (Everyday Discrimination Scale [EDS] [38], victimization scale [48]). Additional preliminary outcomes to be examined will include proximal minority stress (Internalized Homophobia Scale-Revised [49]; two-items assessing outness and concealment [50,51]), community connectedness (LGBT Community Scale [52]), substance use quantity and frequency (Quick Drinking Screen [53] and Alcohol, Smoking, and Substance Involvement Screening Test [WHO-ASSIST] [54]), and PTSD symptom severity (PTSD Checklist for DSM-5 [55]).

**Assessments.** Participants will complete assessments at baseline, posttreatment, and 3-month follow-up that entail an online Qualtrics survey and the telephone diagnostic interview with a master's or doctoral level clinician. Independent assessors, who will be Master's or doctoral level clinicians separate from the study therapists, will administer the C-SSRS and the SCID-5 mood and anxiety modules at each time point and the psychotic and substance use disorder modules at baseline. Independent assessors will be trained by a leading expert in assessment for clinical trials and participate in weekly reliability meetings to increase fidelity and reduce rater drift. Interrater reliability will be calculated for a subsample (10%) of the assessments. Assessors will confirm participants' location and will be provided with the participants' current address, emergency contact, and nearest emergency room (collected at consent) to enable required actions if a participant endorses acute suicidal risk and it is determined clinical intervention is required. Participants who are deemed high acute risk at the baseline assessment will not be randomized for treatment and will be connected to emergency resources. Participants will be paid $75 for the baseline assessment and $50 for the posttreatment and 3-month follow-up assessments.

See Table 1 for list of measures and assessment time points.

**Table 1 tbl1:** Assessment measures and timepoints.

	Time of Administration		
	Baseline	Post-treatment	3-month follow-up
**Screening and Primary Treatment Outcomes**			
SCID-5 modules [40]:			
Mood disorders	X	X	X
Anxiety disorders	X	X	X
Psychotic disorders	X		
Substance use disorders	X		
Columbia Suicide Severity Rating Scale (C-SSRS) [39]	X	X	X
Patient Health Questionnaire (PHQ-9) [36]	X	X	X
Generalized Anxiety Disorder Scale (GAD-7) [37]	X	X	X
**Psychological Measures and Secondary Treatment Outcomes**			
Everyday Discrimination Scale (EDS) [38]	X	X	X
LGBTQ + Victimization [48]	X	X	X
Life Events Checklist (LEC) [47]	X		
PTSD Checklist for DSM-5 (PCL) [55]	X	X	X
Outness & Concealment [50,51]	X	X	X
LGBT Community [52]	X	X	X
Internalized Homophobia Scale (IHS) [49]	X	X	X
Quick Drinking Screen (QDS) [53]	X	X	X
Alcohol, Smoking, and Substance Involvement Screening Test (WHO-ASSIST) [54]	X	X	X
Depression, Anxiety, and Stress Scale (DASS-21) [46]	X	X	X
**Feasibility and Acceptability**			
End-of-treatment interviews		X	
Client Satisfaction Questionnaire (CSQ-8) [41]		X	

### Interventions

3.4

#### EWMS

3.4.1

The EWMS protocol will consist of three, 60-min sessions delivered by a clinician (either in-person or via telehealth, based on veteran's preference). The intervention will begin with brief psychoeducation about expressive writing and psychoeducation on sexual minority stressors and common reactions to these stressors. Participants will be provided with a structured prompt for the expressive writing portion of the sessions where they will be asked to write for 30 min about the most upsetting event that has happened to them related to their sexual orientation for the 3 sessions. The writing prompts will be revised throughout the case series portion of the study to ensure cultural relevance to sexual minority veterans. Following the writing exercise, the clinician will check in with the participant about how the writing went and how it felt to write about the chosen stressor.

#### Control condition

3.4.2

The control writing condition will also be a 3-session individual intervention involving a writing exercise each session. For the control writing exercises, participants will be asked to write for 30 min about their daily activities since waking up that day in a manner that is similar to Pennebaker's neutral writing condition (expressing no thoughts or feelings about the daily activities) [19]. Individuals in the control condition will also be given information about the purpose of the writing exercises to be comparable to the psychoeducation information provided in EWMS. Like EWMS, the clinician will check in with the participant about the writing session, such as asking how the session went and how it felt to complete the writing.

#### Study clinician training

3.4.3

For Phase II, at least 3 clinicians from mental health clinics at [masked] will be trained in EWMS and the control condition in a half-day training. The PI will provide training and weekly consultation to study clinicians, who will be master's or doctoral level clinicians, operating under licensed oversight from the PI. The PI will review session recordings of each clinician's first case after each session and prior to the next session to ensure compliance with protocol. Additionally, the PI will intermittently review sessions thereafter to ensure fidelity to the protocol is maintained. The PI is a licensed clinical psychologist and will be informed about any clinical worsening, presence of suicidal ideation or adverse events in weekly supervision. The PI will be alerted in situations of high acute risk to help, if needed, in connecting participants to emergency resources.

### Power analysis

3.5

Consistent with recommendations for pilots, the purpose of the pilot trial is to examine feasibility and acceptability of the study design and intervention to inform the design of a future, fully powered efficacy trial [56,57]. As such, our proposed sample size is consistent with recommendations for pilot trial sample sizes, 12 to 35 per arm [[58], [59], [60], [61], [62]].

### Analytic plan

3.6

#### Feasibility and acceptability

3.6.1

We will conduct descriptive statistics and data visualizations to describe the feasibility and acceptability data. We will calculate the rate (referrals per month) and total number of referrals, screens, participants who were eligible, participants who were randomized, and participants who completed the assessments. We will calculate retention rates by examining the number of eligible participants who completed all study procedures. For feasibility of the intervention, we will examine percentage of treatment completion across participants. Regarding acceptability, we will conduct descriptive statistics and data visualizations to describe scores on the CSQ-8 [41] and the EBPAS-50 [42].

To inform necessary modifications to the EWMS protocol, we will conduct rapid content analysis on the exit interviews, which allows for a quick and accurate reduction of qualitative data and produces results useful for efficient intervention refinement [45]. In this approach, data analysis occurs concurrently with data collection. As interviews become available, they will be reviewed and summarized by members of the research team using structured templates organized by key topics from the interview guides and will include information on emergent topics. Analysis will be conducted by a team of 3 at minimum. We will transfer the summaries into matrices and use matrix analysis methods to identify key themes from the interviews. Matrices streamline the process of summarizing data to enable identification of similarities, differences, and trends in responses across interviews, expediting synthesis and summary of findings [63]. As analysis continues, we will identify themes that are evident across multiple interviews. These cross-cutting themes will become the framework for our final analysis, for which we will use a hybrid deductive and inductive analytic approach [45]. We will characterize perceptions of feasibility, acceptability, usefulness, barriers and facilitators to participation, and recommendations for future implementation.

#### Preliminary outcomes and descriptive trend analyses

3.6.2

Because the trial is a pilot study in preparation for a fully powered clinical trial, we will conduct descriptive statistics and data visualizations to describe the data. We will present the means, standard deviations, and ranges for each of the study time points for the PHQ9, GAD7, and DASS subscales, and produce visual plots to display outcomes by group over time. Lastly, we will examine effect sizes for primary outcomes of interest, including the PHQ-9, GAD-7, and DASS, between groups. Effect sizes (Cohen's *d*) will be calculated as the change from baseline to posttreatment and baseline to 3-month follow-up, standardized by the pooled baseline standard deviations for the EWMS and neutral writing condition. This will indicate the magnitude of change at each posttreatment time point.

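### Section 3.6.2 labels Cohen's d a between-group effect but defines and interprets it as change from baseline, with the neutral-writing arm never subtracted

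*Protocol article*

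**What the plan says.** Three consecutive statements in section 3.6.2 of the protocol article define the symptom effect size.

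- The label: "we will examine effect sizes for primary outcomes of interest, including the PHQ-9, GAD-7, and DASS, between groups".
- The formula: the effect size "will be calculated as the change from baseline to posttreatment and baseline to 3-month follow-up, standardized by the pooled baseline standard deviations", with the pooling taken over both arms.
- The interpretation: "This will indicate the magnitude of change at each posttreatment time point".

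Two other places matter. Section 3.2 (Participants) admits veterans with a "score above 10 on the Patient Health Questionnaire-9 [PHQ-9] [36] or the Generalized Anxiety Disorders-7 [GAD-7] [37"], and section 3.3.3 (Measures) repeats that rule. Section 3.3.2 (Screening) has potential participants "complete the baseline assessment (diagnostic interview via phone and online self-report questionnaires) to determine eligibility for the study". The scores that admit a participant are therefore also the baseline from which change is measured.

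Section 3.1 limits the symptom results to preliminary trends and makes feasibility and acceptability the primary outcomes. Section 3.6.2 also plans means, SDs and ranges at each time point, and plots by group.

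**The concern.** The label describes a contrast between arms. The numerator and the interpretation describe change over time, with no arm named and no control change removed. An analyst who follows the formula could report one d per arm, or a difference between two changes, and claim to have followed the plan either way.

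These are different quantities. A within-arm d contains whatever the treatment does, plus natural course, the non-specific effect of three clinician-led sessions, and the fall expected on retest in people admitted because their score was high. The neutral-writing arm is there to remove those extra components. An inert intervention would have a positive expected within-arm d from regression to the mean alone, and an expected difference in change of zero.

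The stake is the next trial. The article says several times that the symptom trends are to inform the design of a fully powered efficacy trial. If a within-arm d were taken as the effect to be detected between arms, that trial would be too small.

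**Working it through.** The plan gives no effect size, SD, correlation, alpha or power, so it has no figure of its own to reproduce. The one arithmetic check available is the arm size: 54 / 2 = 27, inside the 12 to 35 per arm of section 3.5.

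**1. The two readings.** Write E and C for mean improvement (baseline minus follow-up) in EWMS and neutral writing, and S for the pooled baseline SD.

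- Literal reading: d = E / S in one arm (and C / S in the other).
- Difference in change: d = (E − C) / S.

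The label and the two-arm S fit the second. The numerator and the stated interpretation fit the first.

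**2. Regression to the mean under the literal reading.** PHQ-9 and GAD-7 were simulated with no true change and entry if either exceeded 10. Every input below is an assumption.

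| Assumed source population | Same-day errors of the two scales | Retest correlation | PHQ-9 within-arm d |
|---|---|---|---|
| Mean 8 to 12, SD 5.5 (both scales), cross-scale correlation about 0.65 (0.57 at retest 0.6) | independent | 0.6 to 0.9 | 0.03 to 0.22 |
| PHQ-9 mean 8 to 12, SD 6; GAD-7 mean 7 to 10, SD 5.5; true-score correlation 0.7 | independent | 0.6 to 0.8 | 0.08 to 0.28 |
| As the row above | correlated 0.7 | 0.6 to 0.8 | 0.12 to 0.52 |

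In rows 2 and 3 the upper ends come from scores rounded to whole points. The corresponding GAD-7 ranges are 0.05 to 0.19 and 0.10 to 0.43. The sign is positive throughout. The size depends strongly on whether the two self-reports share same-day error, about which the documents say nothing.

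**3. Both readings at 27 per arm** (source mean 10, SD 5.5, retest 0.7, independent errors; average over simulated trials).

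| True between-arm effect | EWMS within-arm d | Difference in change |
|---|---|---|
| 0 | 0.13 | 0.00 |
| 0.30 | 0.43 | 0.31 |

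Subtraction removes the regression component in expectation.

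**4. Planning illustration** (two-sided 0.05, 80% power, normal approximation): n per arm = 2(1.96 + 0.84)² / d² ≈ 15.70 / d².

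- d = 0.30: 175; d = 0.60: 44; d = 0.90: 20.
- d = 0.43 in place of 0.30: 15.70 / 0.185 ≈ 85 per arm. With a true effect of 0.30, power is then Φ(0.30 × √(85/2) − 1.96) = Φ(0.00), about 50%.

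**5. Precision under the difference-in-change reading.** With equal SDs and baseline-to-follow-up correlation r, and S treated as known, the variances in SD units are (2/27) × 2(1 − r) for the change score and (2/27) × (1 − r²) for ANCOVA. Their ratio is (1 + r)/2: 0.75 at r = 0.5 and 0.80 at r = 0.6, a saving of 25% and 20%.

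| r | 95% half-width, change score | 95% half-width, ANCOVA |
|---|---|---|
| 0.3 | 0.63 | 0.51 |
| 0.5 | 0.53 | 0.46 |
| 0.7 | 0.41 | 0.38 |

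When the baseline SD is narrowed by the entry rule the saving is smaller, about 6 to 11% of variance under the assumptions of row 3 in step 2. The chance baseline difference has standard error √(2/27) = 0.27 SD. Given an observed imbalance b, the change score over-corrects by (1 − r)b: at r = 0.5 and b = 0.27, about 0.14 SD.

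**The case against.** The best defence is that the text is condensed, not wrong. It announces a contrast between arms, and a baseline SD pooled over both arms is the usual denominator of a difference-in-change d. On that view the subtraction is an unstated step. Means, SDs and plots by group are also planned, so a reader could probably compute the contrast. No test or progression rule uses d, and no passage says that d will set the next sample size. Baseline adjustment and confidence intervals are commonly left to an analysis plan.

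Much of this stands. The difference-in-change reading is permitted, and it is unbiased under randomisation. Lack of baseline adjustment does not create regression to the mean in a randomised contrast; it costs precision. The limited role of the symptom results lowers the severity.

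It does not remove the inconsistency. The article chose to state a formula and an interpretation, and both depart from the label. This is a stated definition that does not match itself, not a detail left for later.

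A reader might go further and infer that d would mostly measure regression to the mean. The documents do not support that. They give none of the inputs needed to find the share, the share is zero in expectation under one of the two permitted readings, and a within-arm change would also contain natural course, non-specific effects and any treatment effect.

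**Conclusion.** The definition of Cohen's d in section 3.6.2 is internally inconsistent and should be fixed. The literal formula gives a within-arm change that cannot be read as an intervention effect. Its regression component is positive but cannot be sized from the documents; roughly 0.03 to 0.5 baseline SD is a range over assumed means, SDs, retest correlations and error correlations, not an estimate for this trial. The alternative reading is valid but wider than it need be, by an amount that depends on r and on how far the entry rule narrows the baseline SD.

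The severity is should-fix. The analysis is descriptive and secondary to feasibility and acceptability, but it is meant to inform the efficacy trial, and the two readings could lead to very different designs.

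**What to change.** Replace the definition and interpretation in section 3.6.2, or settle them in the analysis plan, along these lines:

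> At posttreatment and at 3 months, the effect is the EWMS minus neutral-writing difference in the outcome, adjusted for its baseline score by ANCOVA. It will be given in raw scale points and divided by the baseline SD pooled over the two arms, with a 95% confidence interval. Change within each arm will be shown as description only and is not an estimate of the intervention effect.

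The cost is a few sentences and one degree of freedom per model. The baseline scores are already collected, so no new data are needed, and the descriptive status of the symptom results is unchanged. The interval will be wide at 27 per arm (half-width about 0.4 to 0.5 SD in the table above), which is itself useful to whoever designs the efficacy trial.
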